### Primary outcomes

The Functional Oral Intake Scale (FOIS) [25] will be the main observational indicator used for the overall evaluation of swallowing function.

### Secondary outcomes

UES residual pressure, evaluated by high-resolution manometry (HRM).UES resting pressure, defined as mean UES pressure calculated as the average of the inspiratory and expiratory values [26], with a reference range between 58 and 109 mmHg, evaluated by HRM.Duration of UES relaxation, evaluated by HRM.Velopharyngeal peak pressure and hypopharyngeal peak pressure, evaluated by HRM.UES opening, video fluoroscopic swallowing study (VFSS) (DBA-300 type remote control dual-bed gastrointestinal X-ray machine, Toshiba, Japan) will be used for evaluation, with the most open part of the cricopharyngeal muscle divided into 4 levels according to the modified barium swallow impairment profile (MBSImP) [27], corresponding to 0 to 3 points, respectively: normal open , 0; partially open, 1; slightly open, 2; and not open, 3.Pharyngeal construction ratio (PCR): evaluated by VFSS. It is the ratio of pharyngeal area at maximal contraction to pharyngeal area at rest [2]. The calculation formula: PCR = PA_max_/PA_hold_ (PA_max_ refers to the minimum area of the pharyngeal cavity when contracting during oral swallowing in the image of the VFSS, and PA_hold_ refers to the maximum area of the pharyngeal cavity with a 1 ml bolus in the patient’s mouth in the resting state). The calculation formula: PCR = PA_max_/PA_hold_ (PA_max_ refers to the pharyngeal area at maximum construction; PA_hold_ refers to the pharyngeal area with the bolus in the “hold” position) [28].Residue of bolus in the epiglottis valley or piriform sinus, evaluated by flexible endoscopic evaluation of swallowing (FEES).Penetration and aspiration, evaluated by VFSS and FEES.

### Participant timeline

The total duration of participation in the study will be 4 weeks. Figure 2 is a schedule of enrollment, interventions, and assessments for all study patients.

**Fig. 2 Fig2:**
[figure not shown]
Schedule of enrolment, interventions, and assessments for all study patients

### Sample size estimates

To detect significant differences between groups using an independent sample *t* test, a sample size of 44 patients is needed, assuming a spontaneous recovery mean ± SD in the late group of 2.6 ± 1.1 [29, 30], and a recovery mean ± SD of 4 ± 1.8 in the early group, as determined by our pilot study. These estimates assume a type I error of 0.05, a power of 0.80, and an estimated 10% rate of loss to follow-up.

### Recruitment

Patients with post-stroke dysphagia admitted to the Department of Rehabilitation Medicine, the Third Affiliated Hospital, Sun Yat-sen University, will be screened by an experienced doctor. In addition, the research information is posted on official accounts of our department. We also actively contact with other hospitals and ask them to refer potential suitable patients to our department. Those who meet the inclusion criteria and provide written informed consent will be enrolled.

### Data collection and management

A clinical research associate will ensure that patient inclusion and data collection are in line with the protocol and will check the following variables: patient initials, date of birth, sex, signed consent form, eligibility criteria, date of randomization, treatment assignment, adverse events, and study endpoints. The data will be collected by the clinical research associate on case report forms. The study documents will be stored and kept in a locked and secure office. All personnel involved in data analysis will be masked. Only the PI and the statisticians will have access to the final data set. If the patient drops out, all data before he/she drops out will be recorded, as well as the reason for the patient’s withdraw and any adverse event.

### Statistical analyses

The statistical analysis will be performed using the Statistical Package for Social Sciences (SPSS) version 23.0 for Windows by a statistician who is not involved in the study. A chi-square test will be used to compare the expulsion rate between the early and late groups. If the expulsion rate of the two groups is not statistically significant (*p* > 0.05), compliance of the groups will be considered similar. On the contrary, it is considered that the compliance of the two groups of patients is inconsistent, and it is necessary to re-recruit research cases, which will be assessed by the Data Monitoring Committee. Normally distributed data will be presented as the mean ± standard deviation. Categorical data will be presented as the frequency and proportions. Assumptions of normality will be tested with the Kolmogorov-Smirnov test. The parametric data will be analyzed by the independent sample *t* test, while the non-parametric data will be analyzed by the rank sum test. The *p* values ≤ 0.05 will be considered statistically significant. A comparison between two groups will be used to assess whether the efficacy (represented by FOIS, UES residual pressure, UES resting pressure, duration of UES relaxation, etc.) is different. A chi-square test will be used to compare the differences in the proportion of patients with improved swallowing function (assessed by FOIS) between the groups. Improvement prior to and post treatment in both groups will be assessed. Efficacy evaluation indicators (FOIS, UES residual pressure, UES resting pressure, duration of UES relaxation, etc.) will be compared two weeks after the first and second injections to assess improvement in the groups. A logistic regression method will be used to establish a probability model of BTX efficacy and influencing factors. The effect of each influencing factor on BTX efficacy (OR and 95% confidence interval) will be quantitatively analyzed to determine the interpretable accuracy and reliability of the coefficient *R*^2^ evaluation of the established efficacy and influencing factors model, with the FOIS score of the BTX group will be defined into effective and non-effective, a two-category variable *Y* (FOIS ≥ 3, *Y* = 1; FOIS<3, *Y* = 0). Patients’ age, gender, stroke lesion location, UES residual pressure, UES resting pressure, duration of UES relaxation, velopharyngeal peak pressure and hypopharyngeal peak pressure, UES opening, pharyngeal construction ratio, residue of bolus in the epiglottis valley or piriform sinus, penetration, and aspiration will be used as influencing factors of variable Xi (*i* = 1, 2, …11). A chi-square test will be used to compare the incidence of adverse events between the groups. An interim analysis will be performed after inclusion of the first 22 patients by a statistician who is not involved in this research. The data collection of the study will be assessed and confirmed by the Data Monitoring Committee, which can make decision to stop the research when it is harmful or futile.

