**Methods:**

BECURE is a single-center randomized, placebo controlled, double-blinded, superiority clinical trial. To detect a significant difference between the 2 groups, a sample size of 44 patients is estimated. The intervention is BTX versus placebo, with 1:1 randomization. The randomization sequence from 1 to 44 was generated using the Statistical Package for Social Sciences. The study is divided into two phases. In the first phase, patients will be injected with BTX or the placebo. In the second phase, patients who received a placebo injection and those who did not respond to the first BTX injection will receive an injection of BTX. The primary outcome is the score of the Functional Oral Intake Scale (FOIS). The secondary outcomes are as follows: upper esophageal sphincter (UES) residual pressure, UES resting pressure, duration of UES relaxation, velopharyngeal and laryngopharyngeal peak pressure, UES opening, pharyngeal construction ratio, residue of bolus in the epiglottis valley or piriform sinus, and penetration and aspiration.

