### Drop out criteria

Participants are found to be unable to complete the follow-up on time, or there is an unpredictable condition such as severe adverse event.Participants require not to participate in this research.

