### Allocation and randomization

The late group will initially act as the control group for the early group but will receive BTX treatment later if no improvement of FOIS is achieved. Qualified subjects will be randomized (1:1) in a double-blind fashion to the early group or late group (placebo-control). The randomization sequence was generated by a statistician using the Statistical Package for Social Sciences. A number from 1 to 44 was randomly generated and the random envelopes were generated according to the randomization sequence. The principle investigator (PI) is enrolling patients. A nurse who does not join in the assessment and treatment of the participants will assign participants to their allocation according to the random envelopes. Throughout the double-blind phase of the study, patients and investigators will not be informed of the treatment-group assignment. The BOTOX and placebo will be provided in identical syringes, allowing double-blinded administration. One nurse will be responsible for the dilution of BOTOX and placebo. Unblinding is permissible if there are any adverse events, or participants request the termination of the trial. When unblinding becomes necessary, the principal investigator (PI) will report the reason for the unblinding of patients and the associated adverse event (if exist) to the Data Monitoring Committee, who will jointly decide whether to unblind or not. Once unblinded, the participating investigators, the patient and his/her family will be informed of the patient’s allocation by the nurse who know the patient allocation. All interventions, examination results, adverse events, and reasons for unblinding will be documented.

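### A chi-square test on 22 patients per arm cannot show that drop-out is similar, and recruiting more patients does not repair outcome-related drop-out

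*Protocol article*

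**What the plan says.** Under Statistical analyses, the protocol article sets a decision rule: "A chi-square test will be used to compare the expulsion rate between the early and late groups". If p > 0.05, "compliance of the groups will be considered similar". If not, "it is considered that the compliance of the two groups of patients is inconsistent, and it is necessary to re-recruit research cases", and the sentence continues: "which will be assessed by the Data Monitoring Committee".

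The article does not define the expulsion rate. The nearest definition is under Drop out criteria: "Participants are found to be unable to complete the follow-up on time, or there is an unpredictable condition such as severe adverse event", or the participant asks to leave. This write-up therefore reads the term as drop-out, which is an interpretation.

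The Sample size estimates section states that "a sample size of 44 patients is needed", which already allows for 10% loss to follow-up. The abstract gives the allocation "with 1:1 randomization", so there are 22 patients per arm. On the sequence, Allocation and randomization says: "A number from 1 to 44 was randomly generated".

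**The concern.** The rule has two branches, and each draws a conclusion that the data cannot support.

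- **Non-significant result.** Failure to reject equality is taken as evidence of equality. With 22 per arm and few expected events, the test will usually be non-significant even when drop-out differs materially. A real imbalance could then be passed over as harmless.
- **Significant result.** The remedy is more patients. If drop-out is related to treatment and outcome, which is plausible when severe adverse events are among its stated causes, new patients are subject to the same process and the missing outcomes stay missing.

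What is at stake is how credibly the FOIS comparison handles missing outcomes, and whether recruitment is extended for a reason that does not help.

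**Working it through.** **Inputs.** From Sample size estimates: means 2.6 ± 1.1 (late) and 4 ± 1.8 (early), type I error 0.05, power 0.80, loss 10%, total 44. From the abstract: 1:1 allocation. From Statistical analyses: chi-square, cut-off 0.05. The arm-specific drop-out rates below are assumptions around the planned 10%; the article gives none.

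**1. The plan's own figure.** The common SD is √[(1.1² + 1.8²)/2] = 1.492 and the difference is 4 − 2.6 = 1.4. A two-sided t test at 80% power needs 18.8, so 19 per arm. Then 19/(1 − 0.10) = 21.1, so 22 per arm and 44 in total. The stated size reproduces and is not in question. Ordinary 10% attrition is already paid for.

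**2. Chance that the rule flags a true imbalance.** All 22 vs 22 tables were enumerated under binomial drop-out, rejecting at p ≤ 0.05.

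| Assumed drop-out | Pearson | Yates | Fisher |
|---|---|---|---|
| 10% vs 10% (false trigger) | 4.3% | 0.4% | 1.4% |
| 5% vs 15% | 18% | 4% | 9% |
| 5% vs 20% | 33% | 11% | 20% |
| 5% vs 25% | 49% | 23% | 35% |
| 10% vs 30% | 39% | 22% | 28% |

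For 80% power the drop-out test would need about 49 per arm (5% vs 25%), 62 (10% vs 30%) or 141 (5% vs 15%).

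**3. A split that would be called similar.** Take 2/22 vs 7/22 (9% vs 32%).

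- Pearson χ² = 44 × (2×15 − 7×20)² / (22 × 22 × 9 × 35) = 532,400/152,460 = 3.49, p = 0.062.
- The difference is 5/22 = 22.7 points. Its standard error is √(0.0909×0.9091/22 + 0.3182×0.6818/22) = 0.117.
- The simple 95% interval is 22.7 ± 1.96 × 11.7, or about 0 to 46 points.

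The rule would call this similar, although the interval reaches a gap of nearly half an arm.

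**4. Stability of the trigger.** At 10% loss the expected drop-outs are 0.10 × 22 = 2.2 per arm, below the usual minimum of 5 for chi-square. For 0 vs 4:

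- Pearson: 44 × (0×18 − 4×22)² / (22 × 22 × 4 × 40) = 4.40, p = 0.036.
- Yates: 44 × (88 − 22)² / 77,440 = 2.475, p = 0.116.
- Fisher: p = 0.108.

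The article does not say which version applies, and here that alone decides the outcome. Even within Pearson, 0 vs 4 triggers and 1 vs 5 (p = 0.079) does not.

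**5. Effect of adding patients.** Let q be an arm's drop-out proportion. The arm mean among patients with outcomes differs from the full arm mean by q × (mean of those observed − mean of those lost). The number of patients does not appear. As an illustration, suppose 2/22 vs 7/22 are lost and lost patients are 1 FOIS point worse in both arms. A comparison of observed values is then biased by (0.318 − 0.091) × 1 = 0.23 points, or 0.23/1.4 = 16% of the planned difference, in favour of the arm that loses more. Doubling recruitment under the same process leaves 0.23 unchanged and shortens the interval around it.

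**The case against.** The strongest reply is that the rule is not automatic. Re-recruitment goes to the Data Monitoring Committee, which the Monitoring section describes as independent of sponsors. Participants stay in hospital throughout, the study lasts 4 weeks, and FOIS is compared two weeks after injection, so loss may be small. At equal 10% loss the trigger fires in at most 4.3% of trials. The primary test, its alpha and the sample size of 44 are untouched.

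Much of this stands and limits the severity. It does not rescue the rule. The text still calls re-recruitment necessary, committee review cannot make added patients recover lost outcomes, and low expected loss makes the test still less informative about similarity. Very large gaps would be caught (1 vs 6 gives p = 0.039 by uncorrected Pearson), but that does not justify reading every other result as similar.

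A reader might infer more than the article supports:

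- **That the trial becomes a comparison of completers.** The article names no analysis set and does not say that drop-outs are excluded. Data collection and management keeps all data recorded before drop-out, with reasons. Analysis sets and missing-data methods may sit in a statistical analysis plan that is not at hand.
- **That added patients would fall outside the randomisation.** The sequence runs only to 44, but it could be extended before further enrolment, and the Monitoring section provides a route for amendments.
- **That type I error is inflated.** Final size would depend on arm-level drop-out counts, not on efficacy results. No inflation has been shown.

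**Conclusion.** The rule is wrong as written. It is an explicit instruction in the article, not a detail left to another document. With 22 per arm, non-significance does not show similar drop-out: gaps of 15 to 20 points from an assumed 5% base are missed in roughly half to two thirds of trials by uncorrected Pearson, and more often by Yates or Fisher. Re-recruitment does not remove bias from outcome-related drop-out.

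The conclusion rests on reading the expulsion rate as drop-out and, for the sizes, on assumed drop-out rates. The 0.23-point bias also assumes that observed values are compared and that lost patients are 1 point worse; it is not an estimate for this trial. That more patients do not remove such bias holds whatever those values are. The point should be fixed. It does not by itself invalidate the primary comparison.

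**What to change.** 1. Delete the inference that p > 0.05 means similar compliance, and delete the re-recruitment clause. Define the expulsion rate or replace it with drop-out as set out under Drop out criteria.
2. Report drop-out and its reasons by arm, with a confidence interval for the difference. The reasons are already collected.
3. State that all randomised patients stay in the week-2 FOIS comparison in their assigned arm, whatever the drop-out comparison shows. The primary method for missing values can be left to the statistical analysis plan.
4. Add a sensitivity analysis for missing week-2 FOIS that is truly unfavourable to BTX. For example, use baseline FOIS or FOIS 1 for missing early-group patients, and a value at or above the observed early-group mean for missing late-group patients. Giving missing late-group patients their own arm's mean would be neutral for them and so not a worst case. Show a milder version alongside, such as baseline FOIS for missing patients in both arms.

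The cost is a wording amendment and a short additional analysis, with no new data. It removes a possible recruitment burden. Trial status reports 10 participants included at manuscript submission; the change should be made without reference to drop-out by arm.

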### Inclusion criteria

Patients are eligible for study participation if they fulfill all of the following criteria:
Meet the diagnostic criteria for stroke, listed in the *Diagnostic criteria of cerebrovascular disease in China (version 2019)* [24].Stable vital signs without severe cardiopulmonary diseaseAged 18–90 yearsFailed in swallowing function improvement after 1 week of balloon dilationFunctional Oral Intake Scale (FOIS) Score ≤ 2Cricopharyngeal muscle cannot completely open, verified by video fluoroscopic swallowing study (VFSS); moderate-severe residue in epiglottic valley or piriform sinus, evaluated by flexible endoscopic evaluation of swallowing (FEES).UES residual pressure > 20 mmHg by high-resolution manometry (HRM).Cooperation with treatment without dysfunction of hearing and comprehension.Provide informed consent on their own behalf (or by legally appointed representatives/authorities).

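### The continuous manometry and fluoroscopy secondary outcomes are compared between arms without using a baseline reading that is already taken, so precision is given up and chance imbalance is left unadjusted

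*Protocol article*

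**What the plan says.** The Statistical analyses section sets the rule for between-arm tests: "The parametric data will be analyzed by the independent sample *t* test, while the non-parametric data will be analyzed by the rank sum test". It applies a two-group comparison to the primary scale and to the manometry measures: "A comparison between two groups will be used to assess whether the efficacy (represented by FOIS, UES residual pressure", followed by UES resting pressure, relaxation duration and an unspecified remainder. The indicators "will be compared two weeks after the first and second injections to assess improvement in the groups". A separate sentence says "Improvement prior to and post treatment in both groups will be assessed".

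No between-arm comparison carries a baseline covariate. The only regression in the section is a different analysis: "A logistic regression method will be used to establish a probability model of BTX efficacy and influencing factors". It models response within the BTX group and estimates no treatment effect.

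The Inclusion criteria require manometry before entry, with "UES residual pressure > 20 mmHg by high-resolution manometry (HRM"), and incomplete cricopharyngeal opening "verified by video fluoroscopic swallowing study (VFSS"). The Secondary outcomes section then lists residual pressure, resting pressure, relaxation duration and the velopharyngeal and hypopharyngeal peak pressures from manometry, and UES opening and the pharyngeal ratio from fluoroscopy.

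**The concern.** Pressures, durations and ratios are measurements on which a patient's own starting value may predict the later one. The plan takes the same view elsewhere: it lists these measures as factors that may influence the effect of BTX. A two-sample test of the week-2 values ignores that information, so all of the between-patient spread stays in the error term.

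In a trial of 44, two things follow. Real effects on sphincter pressure are harder to detect than they need be. And if one arm happens to start with higher pressures, part of that difference is carried into the apparent BTX effect. These outcomes hold the physiological evidence that BTX acts on the sphincter. The point concerns them only, and not the primary FOIS comparison, where entry at a score of 2 or less leaves little baseline range to use.

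**Working it through.** **Inputs.** From the Sample size estimates section: N = 44, means 2.6 (SD 1.1) and 4 (SD 1.8), alpha 0.05, power 0.80, 10% loss. From Allocation and randomization: 1:1, with no stratification stated. Not in the documents and therefore assumed: the correlation r between baseline and week-2 values, taken as 0.3 to 0.7.

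**The plan's own figure.** The pooled SD is √((1.1² + 1.8²)/2) = 1.492 and the difference is 1.4. A two-sided t test at 0.05 needs 19 per arm (power 0.804). Then 19/0.9 = 21.1, rounded up to 22 per arm, or 44. The stated sample size reproduces and is not at issue. After 10% loss, 44 × 0.9 = 39.6, so about 20 evaluable patients per arm.

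**Precision.** Relative to testing week-2 values alone, the variance of the treatment difference is multiplied by

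- ANCOVA: (1 − r²) × (1 + 1/(2n − 4)). The second term is the small-sample price of estimating the slope; with n = 20 it is 1 + 1/36 = 1.028.
- Change scores: 2(1 − r).

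Power is taken from the noncentral t with 38 df (unadjusted or change score) or 37 df (ANCOVA), for effects chosen to have 60% or 70% power unadjusted.

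| r | 1 − r² | SE ratio, √(1 − r²) | ANCOVA power from 60% | ANCOVA power from 70% |
|---|---|---|---|---|
| 0.1 | 0.99 | 0.99 | 59.2% | 69.2% |
| 0.2 | 0.96 | 0.98 | 60.5% | 70.5% |
| 0.3 | 0.91 | 0.95 | 62.8% | 72.8% |
| 0.5 | 0.75 | 0.87 | 71.2% | 80.7% |
| 0.7 | 0.51 | 0.71 | 86.3% | 92.9% |

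The power columns include the small-sample term. Leaving it out raises the 60% column to 64%, 72% and 87% at r = 0.3, 0.5 and 0.7, about one point too favourable.

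**Change scores.** At r = 0.5 the factor is 2(1 − 0.5) = 1, so nothing is gained. At r = 0.3 it is 1.4, and 60% power falls to 46%.

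**Chance imbalance.** The SD of the baseline difference between arms is √(2/20) = 0.316 SD. The probability of an imbalance of at least 0.4 SD in either direction is 2 × P(Z > 0.4/0.316) = 0.206 (0.185 with 22 per arm). Conditional on an imbalance b, the unadjusted estimate moves by r × b. For b = 0.4 this is 0.12, 0.20 and 0.28 SD at r = 0.3, 0.5 and 0.7.

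**Which outcomes have a baseline.** The Inclusion criteria document an entry value explicitly for residual pressure and, as an ordinal grade, for UES opening. For resting pressure, relaxation duration, the peak pressures and the pharyngeal ratio, a baseline is inferred: they come from the same two examinations and are listed as influencing factors. The assessment schedule is in a figure that is not shown.

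**The case against.** The strongest reply is that nothing here is invalid. In a randomized trial the unadjusted test is unbiased over randomizations and keeps its type I error. The outcomes are secondary, and the sample size was set for FOIS. All of that stands.

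The size of the gain also rests on an undocumented correlation. No SD or pilot figure for pressure is given, so a wide spread of pressures cannot be asserted. The entry threshold on residual pressure cuts its range and may lower r for that outcome. This stands too, and is why the gain is shown as a range that reaches nil.

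A third reply is that the sentences on improvement may mean that the arms are compared on change from baseline, which would use the baseline. The wording does not settle this. It does not remove the point, because change scores gain nothing at r = 0.5 and lose power below it. Nor does an unseen analysis plan answer it: the article itself names the test.

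Three stronger readings are tempting and should be resisted. A reader might infer that a baseline imbalance passes in full into the BTX estimate; only r times it does. A reader might infer that the secondary results would be biased or invalid; the documents support only a loss of efficiency and a shift conditional on the imbalance that happens to occur. A reader might extend the point to every fluoroscopy outcome; UES opening is graded 0 to 3 and penetration and aspiration are ordinal or categorical, so linear ANCOVA does not fit them.

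**Conclusion.** The point holds as a nearly free improvement to the analysis of the continuous secondary outcomes: the four kinds of sphincter and pharyngeal manometry measure (residual pressure, resting pressure, relaxation duration, peak pressures) and the pharyngeal ratio. The planned test is valid but does not use information that the trial already collects.

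The benefit is small at r = 0.3 (about 3 points of power), useful at 0.5 (about 11 points) and large at 0.7 (about 26 points, from a base of 60%), with essentially none at 0.2 or below. These figures assume 20 evaluable patients per arm, a linear relation with a common slope, and a correlation that the documents do not supply. For all measures but residual pressure they also assume that the pre-entry examination recorded the value.

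**What to change.** For each continuous manometry or fluoroscopy secondary outcome, replace the unadjusted between-arm t or rank sum test by ANCOVA of the week-2 value on arm and the same patient's baseline value, using log or rank values where the data are skewed. Report the adjusted BTX minus placebo difference with its 95% confidence interval. State that the analysed variable is the week-2 value, so that no choice between raw, change and adjusted analyses is left until the data are seen. Keep UES opening and penetration or aspiration out of this model. Confirm that the baseline value of each covered measure is recorded on the case report form.

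The cost is a sentence of analysis wording and one degree of freedom per test. No new examination is needed, provided those baseline values are recorded. If r turns out near 0.1, the loss is under one point of power.

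### The BTX efficacy model, fitted to BTX patients only, cannot tell factors that predict recovery from factors that change the BTX effect

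*Protocol article*

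**What the plan says.** In the protocol article, Statistical analyses, the stated purpose is "to establish a probability model of BTX efficacy and influencing factors". The outcome is described as "with the FOIS score of the BTX group will be defined into effective and non-effective": Y = 1 for a FOIS score of 3 or more and Y = 0 below 3. Age, sex, lesion location and the manometric, fluoroscopic and endoscopic measures are the candidate factors. Each factor's odds ratio, with its 95% confidence interval, is to be read as its effect on BTX efficacy. The described model contains no placebo data, no treatment term and no treatment-by-factor interaction.

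Four other sections bear on this:

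- Inclusion criteria: every patient enters with a FOIS score of 2 or less.
- Sample size estimates: the calculation proceeds "assuming a spontaneous recovery mean ± SD in the late group of 2.6 ± 1.1", against "a recovery mean ± SD of 4 ± 1.8 in the early group".
- Definitions: late-group patients receive BOTOX at 2 weeks only if their score is still below 3, so the plan provides for some who reach 3 on placebo.
- Treatment or intervention: conventional dysphagia rehabilitation may continue in both arms.

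**The concern.** A patient who starts at FOIS 2 or below and ends at 3 or above has improved, but that alone does not show that BTX caused the improvement. The plan itself expects some improvement without BTX. A factor that raises the chance of recovery equally on BTX and on placebo will show an odds ratio in a BTX-only model. A factor that truly changes the BTX effect will show one as well. Without a comparison arm the two cannot be told apart.

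This does not depend on how many predictors are used or how many patients are enrolled. It would remain with one predictor and a much larger trial. What is at stake is a published list of factors said to influence BTX efficacy, which could be used to choose patients for BTX although the analysis does not show who benefits from it. The population, outcome, cut and interpretation are all stated in the article, so this is a stated analysis that does not answer its stated question. It is not detail left to an analysis plan.

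**Working it through.** **1. The plan's own figure.** The document gives no figure for this model. The inputs used here are the sample size assumptions, so that figure was reproduced first. Difference: 4 − 2.6 = 1.4. Averaged-variance SD: √((1.1² + 1.8²)/2) = √2.225 = 1.492. A two-sided two-sample t test at 0.05 with power 0.80 needs 19 per arm. Allowing for 10% loss, 19/0.90 = 21.1, so 22 per arm and 44 in total. This agrees with "a sample size of 44 patients is needed".

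**2. Some placebo patients must reach the cut.** All start at 2 or below, and the assumed late-group mean is 2.6. On an integer scale a mean above 2 is impossible unless some scores are 3 or more. This step needs no assumption about shape.

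**3. How many.** Assume that 2.6 ± 1.1 and 4 ± 1.8 are week-2 scores; the sample size section gives no time point. Under a normal shape:

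| Arm | Cut at 2.5 (integer scale) | Cut at exactly 3 |
|---|---|---|
| Placebo, 2.6 ± 1.1 | 1 − Φ((2.5 − 2.6)/1.1) = 53.6% | 1 − Φ((3 − 2.6)/1.1) = 35.8% |
| BTX, 4 ± 1.8 | 1 − Φ((2.5 − 4)/1.8) = 79.8% | 1 − Φ((3 − 4)/1.8) = 71.1% |

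Two discrete distributions matched to the placebo mean and SD give 51.3% (discretised normal) and 50.3% (beta-binomial).

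The placebo bounds for any shape on integers 1 to 7 (an assumed range; the article does not state one) come from linear programming:

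- Lowest, 23.8%: probabilities 0.762 at 2, 0.115 at 4 and 0.123 at 5.
- Highest, 75.3%: probabilities 0.2475 at 1, 0.72875 at 3 and 0.02375 at 7.

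Both solutions have mean 2.6 and variance 1.21. If the shape is unimodal, the range is 27% to 63%. If 2.6 were a gain over baseline and not a score, the placebo share would be higher.

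**4. What the planned model would show.** As an illustration, 400,000 patients were simulated with a purely prognostic factor (true odds ratio e¹ = 2.72 per SD in both arms) and a placebo response of 53%.

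| True BTX effect | BTX response | Factor OR, BTX-only model | Interaction OR, both arms |
|---|---|---|---|
| None | 53% | 2.72 | 0.99 |
| Constant log-odds shift of 1.2 | 75% | 2.72 | 1.00 |

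The BTX-only odds ratio is the same whether BTX works or does nothing. The interaction correctly shows no modification in either case.

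**5. Precision of the two-arm alternative.** Evaluable patients: 22 × 0.90 = 19.8, about 20 per arm. For a factor scaled to SD 1, the information on its log odds ratio in one arm is roughly n·p(1 − p). Placebo: 20 × 0.536 × 0.464 = 4.97. BTX: 20 × 0.798 × 0.202 = 3.22. SE of the interaction: √(1/4.97 + 1/3.22) = 0.71. For 80% power: (1.96 + 0.84) × 0.71 ≈ 2.0 on the log scale, an odds ratio of about 7 per SD.

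**The case against.** The strongest defence has five parts.

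- **The model is supplementary.** It is not in the stated objective and is neither a primary nor a secondary outcome. The randomised comparisons of FOIS and of the proportion improved remain, and they carry the efficacy conclusion. This is correct and limits the consequence. But those comparisons estimate an average effect and do not correct the factor odds ratios.
- **Single-arm responder models are common and legitimate.** They are, for predicting outcome after treatment. The article claims more, namely effects of factors on efficacy.
- **The BTX group is not defined.** A reader might infer that the placebo arm is discarded altogether. The text does not settle this, because late-group patients injected at 2 weeks may be included. Their inclusion would not help: they are selected for a score below 3 at 2 weeks and have no concurrent placebo control after that injection. The placebo percentages above would not carry over to them either.
- **The factors found need not be mere predictors of natural recovery.** A reader might infer that the model would report only those. The documents do not support this: true modifiers would also appear, mixed with prognostic factors.
- **The share of effective cases due to natural recovery is uncertain.** Dividing the placebo rate by the BTX rate gives 35.8/71.1 = 50% or 53.6/79.8 = 67%, and a reader might take half to two thirds as the expected share. These are upper limits. They hold only if everyone who would recover on placebo also reaches the cut on BTX. Without that assumption the lower limits are (0.358 + 0.711 − 1)/0.711 = 10% and (0.536 + 0.798 − 1)/0.798 = 42%.

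**Conclusion.** The point stands as a limit on interpretation. A model confined to BTX-treated patients, with an absolute FOIS score of 3 or more as effective, cannot distinguish factors that predict recovery regardless of treatment from factors that modify the BTX effect. That rests only on the stated model, the entry criterion and the assumed late-group mean above 2.

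The size is less certain. The placebo share reaching the cut is 36% to 54% if 2.6 ± 1.1 is a week-2 score with a normal shape, and 24% to 75% for any shape on an assumed 1 to 7 integer scale. A single figure of about half should not be quoted without that range, because it depends on the assumed shape, the scale range and the time point. The primary comparison and its sample size are not affected.

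**What to change.** Relabel the model as predictors of swallowing outcome after BTX injection, state which patients the BTX group contains, and draw no conclusion from the model on who benefits from BTX. This changes wording only and needs no new data.

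If a statement on factors influencing BTX efficacy is wanted, fit both randomised arms at week 2, with FOIS of 3 or more (or the score) as outcome, an arm term, and an arm-by-factor interaction for one or two prespecified factors. Only the interaction should be described as an influence on BTX efficacy, and it should be labelled exploratory. This is more than a wording change, because it alters the model's population, its terms and the factor list, and it fixes the time point.

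The cost in both cases is a weaker claim. At this sample size the interaction analysis would detect only a very large modification, an odds ratio of about 7 per SD for 80% power, so a null result would say little.
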